### Economic evaluation

The economic evaluation aims to determine the cost-effectiveness of the intervention compared with usual care from the employer’s perspective. In addition, a cost-benefit analysis will be performed from the employer’s perspective. Analyses will be performed according to the intention-to-treat principle with multiple imputation of missing data [62, 63]. Sensitivity analyses will be done to assess the robustness of the results. The total employer’s costs of the intervention will be estimated and compared between the intervention and control groups. The 95% CIs will be estimated using approximate bootstrap CIs [63]. For the cost-effectiveness analysis, incremental cost-effectiveness ratios will be calculated by dividing the mean difference in costs between both groups by the difference in effects on the primary outcome measures self-rated physical exertion and MSP. Cost-effectiveness planes will be graphically presented [62]. In addition, a cost-benefit analysis will be performed in which the incremental intervention costs will be compared with the incremental productivity-related costs. This will be expressed as return on investment as well as benefit-to-cost ratio.

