#### Questionnaires

The questionnaires contain standard and validated measures. They include sociodemographic information (i.e., sex, ethnicity, work-related factors [seniority, weekly working hours]), health and behavior (i.e., MSP) [34], medicine use, smoking, general health [35], self-efficacy [36], fear avoidance [37], well-being [38], self-rated physical capacity (aerobic fitness, muscle strength, balance, endurance, flexibility) [39], stress [40] and work environment factors (i.e., perceived physical exertion during work) [41], pain-related work interference [34], noise, psychosocial work environment measured by the Danish Psychosocial Questionnaire (new questionnaire that is currently in the process of being published), work ability [42], need for recovery [43], and sickness absence and presenteeism [44–46].

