### Economic measures

#### Health-related production loss

Presenteeism (reduced performance while being present at work) and absenteeism (hours and days missed from work due to sickness absence) will be measured by questionnaire every 4 weeks [44, 45]. In addition, sickness absence data (absenteeism) will be retrospectively collected from company records after the last follow-up measurement.

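### The employer cost comparison names no adjustment for baseline absence and presenteeism, which would make the productivity-cost difference more precise at little cost

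*Protocol article*

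**What the plan says.** Under Economic evaluation, the protocol article describes the comparison of costs in three places:

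- Totals: "The total employer’s costs of the intervention will be estimated and compared between the intervention and control groups".
- The ratio: "incremental cost-effectiveness ratios will be calculated by dividing the mean difference in costs between both groups by the difference in effects", the effects being those on the primary outcomes.
- The cost-benefit analysis: "the incremental intervention costs will be compared with the incremental productivity-related costs", reported as return on investment and benefit-to-cost ratio.

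On uncertainty it adds "The 95% CIs will be estimated using approximate bootstrap CIs" and "Sensitivity analyses will be done to assess the robustness of the results", without listing those analyses. It names multiple imputation, but no covariate or model for costs.

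Under Cost measures, absenteeism and presenteeism are valued at the participants' salaries. On how they are measured:

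- Health-related production loss says that both "will be measured by questionnaire every 4 weeks", and that "sickness absence data (absenteeism) will be retrospectively collected from company records after the last follow-up measurement". It gives no look-back period for the records.
- The item list under Questionnaires ends with "and sickness absence and presenteeism".
- Data collection says that an electronic questionnaire goes to all participants at baseline, and that baseline fell after randomisation but before the workshops.

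**The concern.** Absence and presenteeism tend to persist within a worker, and perhaps within an institution. Where a pre-intervention value exists, part of the spread in follow-up productivity cost can be predicted from it. A contrast that does not use it leaves that spread in the standard error.

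This trial has about 16 institutions, stratified on size only, so nothing in the design balances habitual absence. Productivity cost enters the cost-effectiveness ratio, and return on investment and the benefit-to-cost ratio set the programme's cost directly against the productivity-cost difference. Noise in that one quantity therefore reaches every economic result.

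A second, smaller consideration is selection. Workers joined the evaluation voluntarily, baseline followed randomisation, and the article's Strengths and limitations section accepts that allocation was not concealed and that selection bias is a risk. Imbalance among the analysed workers could then exceed chance.

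**Working it through.** **Inputs from the protocol article (Power calculation).** Power 0.80, alpha 0.05 (taken as two-sided), SD 2.41, effect 1 point, cluster size 12, intracluster correlation (ICC) 0.005, 96 workers per arm, about 16 clusters. Institutions were drawn in pairs (Randomization and blinding), so about 8 v 8 is derived, not stated.

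**Assumptions (not in the document).** The correlation r between a worker's baseline and follow-up productivity cost is 0.3 to 0.6. The ICC for costs is 0.005 to 0.10; the stated 0.005 is for exertion.

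**Step 1. The stated sample size.** Per arm before clustering: 2 × [2.41 × (1.960 + 0.842)]² = 91.17. Design effect: 1 + 11 × 0.005 = 1.055. Per arm: 91.17 × 1.055 = 96.19, so 192.4 in total and 16.03 clusters of 12. The stated 192 reproduces. The article gives no figure for the cost comparison.

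**Step 2. Standard error (SE) of an arm difference, in SD units.** SE = √[2 × (1 + 11 × ICC)/96]. The same formula gives the spread of the chance difference at baseline.

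| ICC | SE | Probability that baseline imbalance exceeds 0.2 SD |
|---|---|---|
| 0.005 | 0.148 | 18% |
| 0.05 | 0.180 | 27% |
| 0.10 | 0.209 | 34% |

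**Step 3. What imbalance does to the unadjusted difference.** About r times the imbalance carries over. An imbalance of 0.2 SD carries 0.3 × 0.2 = 0.06 to 0.6 × 0.2 = 0.12 SD, which is less than one SE (0.148 SD) even at the lowest ICC.

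**Step 4. Gain from adjustment.** If institution effects persist no more strongly than individual values do, the variance is multiplied by 1 − r² and the SE by √(1 − r²).

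| r | Variance cut | SE cut | Adjusted SE, ICC 0.005 | Adjusted SE, ICC 0.05 |
|---|---|---|---|---|
| 0.3 | 9% | 5% | 0.141 | 0.171 |
| 0.5 | 25% | 13% | 0.128 | 0.156 |
| 0.6 | 36% | 20% | 0.148 × 0.8 = 0.119 | 0.180 × 0.8 = 0.144 |

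**Step 5. Sensitivity to institution-level persistence.** Let c be the correlation of institution effects between baseline and follow-up, and w = (r − c × ICC)/(1 − ICC) the within-institution correlation. With a slope of about r, the remaining fraction of variance is

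[ICC × (1 − 2rc + r²) + ((1 − ICC)/12) × (1 − 2rw + r²)] / [ICC + (1 − ICC)/12].

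At ICC 0.05 and c = r this returns cuts of 9%, 25% and 36% for r = 0.3, 0.5 and 0.6. At c = 1 it gives 24%, 43% and 53%. For example, at r = 0.3, w = (0.3 − 0.05)/0.95 = 0.263, and (0.0245 + 0.0738)/0.1292 = 0.76. The larger cuts need institution effects that are almost perfectly stable.

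**Step 6. Skewed costs.** A simulation used lognormal costs, 8 v 8 institutions of 12 and 3,000 runs per setting, with correlations set on the log scale and institution-level correlation 0.8.

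| ICC | SE at r = 0.3, unadjusted to adjusted | SE at r = 0.5, unadjusted to adjusted |
|---|---|---|
| 0.005 | 0.150 to 0.145 (3% less) | 0.146 to 0.131 (10% less) |
| 0.05 | 0.167 to 0.158 (5% less) | 0.168 to 0.145 (14% less) |
| 0.10 | 0.187 to 0.172 (8% less) | 0.187 to 0.158 (16% less) |

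The mean error was at most 0.01 SD both with and without adjustment, so neither estimator is biased under randomisation.

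**The case against.** The strongest reply is that the article never calls the cost difference unadjusted. A mean difference is the ordinary numerator of a cost-effectiveness ratio, and a regression-adjusted one fits the description equally well. Covariates may be fixed in an analysis plan that is not shown, and the planned sensitivity analyses might include adjustment. This stands: the article neither states nor excludes adjustment, and a reader who infers that it was ruled out goes beyond the text. What remains is that the described method can be improved with data apparently in hand.

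A reader might also infer that chance differences in habitual absence bias the result, to be reported as a saving or loss due to the programme. The documents do not support that. Institutions were randomised, and chance imbalance is sampling error that an interval respecting the institutions would cover. Nor is a change of sign shown: the amount carried over in step 3 is below one SE, so it could reverse only a difference already lost in noise.

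Baseline availability is also partly inferred. Only absence due to musculoskeletal pain is explicitly measured from baseline (Secondary outcome measures). For all-cause absence and presenteeism it follows from reading Questionnaires, Data collection and Health-related production loss together. Access to company records from before randomisation is not described.

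On selection, the article replies that workers were told only their start date and not that any group was a control. That reduces the risk, but the article itself still plans to check for selection.

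**Conclusion.** The point holds as a recommended improvement in precision; no error in the plan is shown. Under the assumed r of 0.3 to 0.6, baseline adjustment would cut the variance of the productivity-cost difference by about 9% to 36% (SE by about 5% to 20%). For skewed costs at ICC 0.005 the SE gain is nearer 3% at r = 0.3 and 10% at r = 0.5. Variance cuts near the top of the 24% to 53% range in step 5 should not be quoted without the assumption of nearly perfect persistence of institution-level absence, for which the document gives no evidence.

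The protection against selection imbalance is real but cannot be sized from the document. Programme costs such as workshops, consultants and materials do not depend on baseline absence, so only the productivity component changes. The article gives no cost figures, so the effect on return on investment cannot be stated in money.

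**What to change.** In the Economic evaluation section, or the analysis plan behind it:

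1. Estimate the arm difference in productivity cost by regression adjusted for the worker's baseline absence and presenteeism.
2. Use that adjusted difference in the cost-effectiveness ratio, the plane, return on investment and the benefit-to-cost ratio.
3. Report the unadjusted difference as a sensitivity analysis.
4. Where data access permits, start the planned company-record extraction at a fixed date before randomisation and use that absence as the covariate for absenteeism cost. Unlike the questionnaire baseline, it cannot be influenced by knowledge of allocation.

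If adjustment is already intended, one sentence saying so settles items 1 to 3.

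The cost is a little more analysis work and, for item 4, an earlier start date and confirmation that access covers the period. No new participants, visits or questionnaires are needed. Recent hires will have a shorter pre-period, which a rate per month employed can handle.

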### Process evaluation

The interpretation of interventions implemented in workplaces can be a challenge. A mere effect evaluation explains only a fraction of the causal assumptions in the program logic [8, 64], and the effect evaluation itself risks rejecting the hypothesis underlying the program theory due to implementation failure (type III error). Thus, both the effects and the implementation (processes) need to be evaluated. Analyzing the effects and processes of an intervention requires a comprehensive evaluation [65].

A process evaluation will be performed, inspired by the framework by Steckler and Linnan [20] to gain insight into the extent to which the intervention is implemented as intended [65]. The implementation will be measured through dose delivered (the amount of intervention components delivered by the consultants) and dose received (employees’ participation in the activities) [20]. The delivery will be measured by asking the consultants to what extent they have followed the specific intervention activities in accordance with the defined criteria written in the intervention protocol (they will fill out a questionnaire after each activity). To check the quality of the consultants’ responses to the questionnaires, observations of the workshops by an independent observer will be conducted (by filling out a similar questionnaire). The dose will be measured by participation percentage and by questionnaires to the participants, after the intervention, asking about their appraisal of the intervention [20]. Moreover, information about the context will be collected through questionnaires from the managers of each of the childcare institutions (e.g., whether there have been any great organizational changes throughout the project period and whether there have been any concurrent activities in both the intervention and control groups that might influence both the implementation and the effect of the study).

### Statistical analyses

Baseline characteristics will be described by questionnaires and the anthropometric measures. Analyses regarding the effectiveness of the primary outcomes and secondary outcomes will be performed after 4 months of intervention with multilevel analyses. Multilevel analyses take clustering of observations of workers within the same team into account, as well as repeated measurements within one participant [66]. All analyses will be performed according to the intention-to-treat principle, including all eligible randomized participants without imputations because mixed models inherently account for missing values [67]. Both the immediate intervention group and the delayed intervention group will be followed with questionnaires and objective measurements after the delayed intervention group has received the intervention. It is expected that during this time, the immediate intervention group will continue with the intervention activities. This allows for longer follow-up for the immediate intervention group and the possibility to do a secondary analysis of long-term follow-up. However, due to the design of the study (two-arm cluster-randomized design employing a wait-list control), no untreated control group exists at the measurement after 8 months, and follow-up effects will thus be uncontrolled and modeled using data from intervention participants only (Fig. 1).

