## Methods/design

### Study design and participants

In clinical intervention research, the randomized controlled trial (RCT) is considered the gold standard. However, in workplace settings, individual randomization cannot always be accommodated [28]. Therefore, this study uses a cluster-randomized design employing a wait-list control, with childcare institutions forming the clusters. Another concern in the workplace is that the introduction of control groups not receiving the intervention can hamper implementation due to impaired organizational commitment [29, 30]. Offering the intervention to the control group after the intervention has been implemented in the intervention group could be a solution for this. Therefore, childcare institutions are randomly assigned to two different arms (immediate/delayed intervention) (Fig. 1). All childcare workers from the randomized institutions were eligible for participation in the intervention, but participation in the evaluation of trial was voluntary. Before entering the trial, all childcare workers were asked to sign informed consent forms. The project began in the second half of 2017 with recruitment of participants, baseline measurements, and initial intervention meetings. This protocol conforms to the Consolidated Standards of Reporting Trials (CONSORT) guidelines [31], and future results of the study will be reported according to these guidelines.

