#### Randomization and blinding

All childcare institutions gave initial agreement to participate before we did the randomization. Because the intervention is group-based, and to avoid contamination between workers, cluster randomization was performed, with each childcare institution constituting a cluster. The randomization was balanced on institution size. Childcare institutions with 9–24 workers were stratified according to size to include an equal number of small (9–12 workers) and large (12+ workers) institutions. Within each size grouping, institutions were randomly allocated to either group 1 (early participatory ergonomics intervention) or group 2 (initial control group and late participatory ergonomics intervention group). The study was dimensioned to enroll approximately 200 workers (*see* the “Power calculation” section below). Because there were 29 institutions willing to participate with a total of approximately 400 workers, not all institutions could be offered an opportunity to participate in the study. In case some institutions dropped out before baseline data collection, we chose to randomize all 29 institutions so that we could replace that institution with another comparable institution. Thus, each institution was assigned a randomly drawn unique priority number between 1 and 100 and subsequently ranked within each group (InterventionSmall, ControlSmall, InterventionLarge, ControlLarge) with smaller number equaling higher priority. Finally, pairs were drawn until we reached the desired number of workers as demanded by the power calculation.

An independent data manager performed a computer-generated randomization using SAS for Windows statistical software (SAS Institute, Cary, NC, USA) developed by an independent statistician. Blinding of participants is not possible, owing to the nature of the trial. However, data collection will be performed using text messages, and persons collecting/handling data will be blinded to group allocation.

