**Fig. 3 Fig3:**
[figure not shown]
Overview of intervention activities and materials used in the intervention. The intervention is an organizational intervention, meaning that the activities are carried out in working teams. The intervention consists of three workshops covering different themes. Between the workshops, the working groups are expected to implement the suggested solutions according to the action plan. The methods vary between plenary discussions and smaller-group discussions in teams. A variety of materials are used throughout the intervention

All included childcare workers at the institutions will be involved in the participatory ergonomics, and the ergonomic consultant will guide the process. At the first workshop lasting 3 hours, the workers will identify work tasks that entail high physical workload that they perceive as risk factors for MSP and will analyze them. The results of this workshop should be three or four prioritized work tasks that should be (1) relevant (e.g., many workers perform the task, or the task is done many times during a working day) and (2) entail high physical workload or high physical activity. Further, the workers are asked to find solutions to the prioritized work tasks and make an action plan. They are again asked to prioritize the solutions according to (1) efficiency (i.e., can this solution reduce physical workload, physical exertion, and MSP?), (2) feasibility (i.e., is this solution likely to be implemented within the project period?), and (3) integration with the core work task (i.e., can this solution also improve the performance of the core work task?). After the workshops, the solutions should be implemented. At two follow-up meetings lasting 1.5 hours each, the implementation of the solutions will be evaluated, and possible adjustments will be made. If the workers find the implementation of a solution successful, the solution will be recommended for permanent adoption.

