#### Power calculation

For the power calculation, we used the calculation for a clustered parallel group with before-and-after measures to calculate the design effect [60]. Statistical power analysis was performed for primary outcome measures. The scale for self-rated physical exertion (0–10) has a mean of 4.09 and an SD of 2.41 in a representative sample of childcare workers in Denmark (*N* = 1137) [5]. The intracluster correlation coefficient (ICC) was calculated on the basis of a previous participatory ergonomics intervention among eldercare workers [61]. With a power of 0.80, an alpha of 0.05, a fixed cluster size of 12, and an estimated ICC of 0.005, we need 192 participants (96 per group) corresponding to approximately 16 clusters to statistically demonstrate a relevant effect in physical exertion of 1 point [60]. We also tried to vary the cluster size between 9 and 20 and check for differences in changing the values of ICC, which did not change the anticipated power very much. Because this is an organizational intervention, we expect only a small number of dropouts. In addition, the intervention period is quite short. We therefore expect to include 10% more than needed according to our power calculations, so that at baseline we will include approximately 210 participants. Additional power calculation for MSP showed that the numbers needed are within the same range as calculated for physical exertion.

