### Strengths and limitations of the study

The cluster-randomized controlled trial design is a methodological strength because it minimizes the risk of contamination between the intervention and control groups and reduces the risk of bias. The systematic intervention mapping approach is a strong feature of the study. The experience and information obtained in the process of tailoring and developing the intervention will be captured and, hopefully, benefit both the present and future studies. Another strength is the monthly monitoring of the outcomes. Moreover, as recommended by Takala and colleagues, we will use multiple tools to capture different aspects of physical workload [56]; such as objective measurements, observations, and questionnaires. This will also allow a rigorous description of the physical workload and physical activity at work in this occupational group. By also incorporating a process evaluation, we will gain insight into the implementation process within the intervention teams and into potential parallel activities in control teams. Another strength is that consultants will deliver the intervention, and these consultants are not involved in the evaluation. The results should be generalizable to similar workplaces, and we will conduct an economic evaluation to evaluate the cost from an employer’s perspective.

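### The effect analyses are described as allowing for clustering by team, but institutions were randomised; the institution should be named as a level of the model

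*Protocol article*

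**What the plan says.** The protocol article is consistent about the design. Under Study design and participants, "this study uses a cluster-randomized design employing a wait-list control, with childcare institutions forming the clusters". Under Randomization and blinding, "cluster randomization was performed, with each childcare institution constituting a cluster". The power calculation arrives at "192 participants (96 per group) corresponding to approximately 16 clusters", using clusters of 12, which is the size of an institution (9-24 workers), not of a small group inside one.

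Only one sentence, in Statistical analyses, says which clustering the effect models handle: "Multilevel analyses take clustering of observations of workers within the same team into account, as well as repeated measurements within one participant". It covers the primary and the secondary outcomes. The section calls the trial cluster-randomised but does not name the institution as a level.

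The word *team* is used in two ways elsewhere. The Fig. 3 caption sets teams against the plenary: "The methods vary between plenary discussions and smaller-group discussions in teams". There a team is a subgroup of those attending. Strengths and limitations uses it more loosely, promising insight "into the implementation process within the intervention teams and into potential parallel activities in control teams", where a team could be a whole workplace. Nowhere are team and institution equated, and the number of teams per institution is not given.

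**The concern.** The arm is assigned to institutions, so the arm contrast is subject to whatever variation exists between institutions. Workers in one institution share a manager and plenary workshop sessions, so their outcomes may move together across teams. A model with random effects for team and worker only has no place for that shared variation. It counts the teams of one institution as separate replicates, and it can credit the arm contrast with more information than about 16 institutions supply (16 - 2 = 14 degrees of freedom for a comparison of institution means).

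At stake is the validity of the test of arm in every effect analysis, if the sentence is followed literally. A protocol may leave the random-effects structure to the analysis plan. This one states a level, and the level differs from the randomised unit.

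**Working it through.** **Inputs from Power calculation.** "With a power of 0.80, an alpha of 0.05, a fixed cluster size of 12, and an estimated ICC of 0.005". The exertion scale "has a mean of 4.09 and an SD of 2.41". The target difference is 1 point. Sidedness is not stated; two-sided 0.05 reproduces the figure.

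**Step 1: reproduce the plan's sample size.**
- Without clustering: n per arm = 2 × [2.41 × (1.960 + 0.842) / 1]² = 91.17.
- Design effect for clusters of 12: 1 + (12 - 1) × 0.005 = 1.055.
- With clustering: 91.17 × 1.055 = 96.19 per arm, and 96.19 / 12 = 8.02 clusters per arm.

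This matches 96 per group and about 16 clusters; power at 96 per arm is 0.799. The sample size therefore already treats institution-sized groups as the clusters.

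**Step 2: error from modelling teams only.** Assumptions, none of which the document gives: 2, 3 or 4 equal teams per institution of 12 (team size s = 6, 4 or 3); all clustering at institution level; one outcome per worker; and ICCs above 0.005.
- True variance factor: 1 + 11 × ICC.
- Factor used by a team-only model: 1 + (s - 1) × ICC.
- SE ratio r = √(true / used).
- Large-sample type I error = 2 × [1 - Φ(1.96 / r)].

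Example, ICC 0.05 with 3 teams of 4: true 1.55, used 1.15, r = √1.348 = 1.161, type I error 9.1%.

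| ICC | True factor | Factor used (2 / 3 / 4 teams) | SE ratio | Large-sample type I error | Simulated type I error |
|---|---|---|---|---|---|
| 0.005 | 1.055 | 1.025 / 1.015 / 1.010 | 1.015-1.022 | 5.3-5.5% | 4.1-4.6% |
| 0.02 | 1.22 | 1.10 / 1.06 / 1.04 | 1.053-1.083 | 6.3-7.0% | 5.3-6.4% |
| 0.05 | 1.55 | 1.25 / 1.15 / 1.10 | 1.114-1.187 | 7.8-9.9% | 7.1-9.4% |
| 0.10 | 2.10 | 1.50 / 1.30 / 1.20 | 1.183-1.323 | 9.8-13.8% | 9.8-13.8% |

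The simulation used 16 institutions of 12 and 40,000 trials per scenario, with the team variance floored at zero and t tests on team-level degrees of freedom. At ICC 0.005 the team-only test is slightly conservative, because the floor offsets the small inflation.

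**Step 3: institution as the unit.** In the same simulated trials, a t test on institution means with 14 degrees of freedom rejects in 4.8-5.2% at every ICC tried.

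**The case against.** The strongest reply is that *team* means the workplace. Process evaluation says that concurrent activities in both arms are reported by institution managers; Strengths and limitations then speaks of parallel activities in control teams, which looks like the same information. If Statistical analyses uses the word in that way, the type I error stays at 5% and one word is loose. This is plausible and cannot be ruled out. But the Fig. 3 caption points the other way, and no text settles it.

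Second, the sentence describes multilevel methods in general and does not exclude an institution level. That is true, and the full analysis plan may specify one. It remains the only level of grouping above the worker that the article names for its effect models.

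Third, a reader might infer that the primary tests are in fact too liberal. The documents do not support that. At 0.005, the only ICC stated, there is no practical inflation; the marked inflation needs ICCs 10 to 20 times larger. Placing all clustering at institution level also gives the widest gap between the two models, since any share arising within teams would be captured by the team effect.

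Fourth, the calculation uses one outcome per worker, while the plan has a baseline and 4-weekly measures. In a change or arm-by-time contrast a stable institution effect largely cancels, and what matters is how far institutions differ in their change over time. This stands: the rates above are illustrative, and an institution random intercept alone would not cover that component.

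Finally, a reader might count the absence of a degrees-of-freedom method as an error. It is normal analysis-plan detail and is not one.

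**Conclusion.** The mismatch is real: the trial is randomised and powered by institution, while its analysis section names team as the clustering level. Whether it does harm depends on two things the document does not settle: that a team is a sub-unit of an institution, and that institutions differ in the tested contrast by clearly more than an ICC of 0.005 implies. With both, and under the assumptions listed in the check, type I error could reach roughly 8-10% at ICC 0.05 or 10-14% at ICC 0.10. At the protocol's own ICC the standard error would be only 1.5-2.2% too small. That ICC was borrowed from an eldercare study, and the validity of the arm test should not depend on its being right for childcare. The size applies to a continuous outcome such as exertion; the second primary outcome, pain, has several components and was not examined separately. This is an inexpensive correction to make before analysis, not evidence that the planned tests are invalid.

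**What to change.** In Statistical analyses, state that all effect models include the institution, as the unit of randomisation, as a random level, together with the worker; team may be added, nested within institution. The institution level must act on the contrast being tested: with an arm-by-time or baseline-adjusted comparison this means, for example, an institution-by-time term and not only an intercept. A small-sample degrees-of-freedom method suited to about 16 clusters (Kenward-Roger or Satterthwaite) is advisable and can sit in the analysis plan. If *team* was meant as institution, replace the word.

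The cost is one sentence and a small change to the model code. No new data are needed. Confidence intervals may become slightly wider, and the sample size stays as it is because it already uses clusters of 12.
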